**17-1-1-2. Test for Brain Motor Processing**

To assess brain motor processing, motor threshold and motor evoked potentials will be measured using the TMS MagPro X100 device. Generally, the goal of motor evoked potentials is to evaluate the motor nervous system by applying a single stimulating pulse through transcranial magnetic stimulation to the motor cortex and then recording this motor stimulation from the corresponding muscle using electromyography electrodes. The recorded wave is known as the motor evoked potential.

Motor threshold will also be an index of cortical excitability and will be used to determine the intensity of stimulation with the device.

In this test, four variables (active motor threshold and amplitude of motor evoked potentials for the multifidus muscle and abdominal transverse) will be examined. These variables are indicators of excitability, performance, and the integrity of neural pathways and corticospinal areas related to these muscles.

For recording variables related to the multifidus muscle, the patient will sit comfortably on a chair with their feet on the ground. A surface electromyography electrode will be placed on the spinous process of L5, aligned with a line connecting the PSIS and the L1-L2 space. The ground electrode will be placed on the iliac crest. The bandwidth will be set from 5 to 500 Hz. To achieve maximal contraction in the multifidus muscle, the participant will be asked to perform a trunk extension against resistance and hold it for 3 seconds. This movement will be repeated 3 times, and the maximum contraction will be measured based on the Root Mean Square (RMS) within a 1-second window. Then, 20% of this value will be used as the submaximal contraction, which will be displayed on a monitor for the participant to maintain throughout the recording. This contraction is intended to facilitate the recording of motor evoked potentials in the paravertebral muscles. In other words, if the muscle is in a resting state, recording will be difficult.

To record variables related to the abdominal muscles, the patient will sit comfortably on a chair with their arms resting on the chair and knees apart. The surface electromyography electrode will be placed 2 cm below and 2 cm inward from the ASIS, which are the most superficial parts of these muscles, and the ground electrode will be placed on the iliac crest. The bandwidth will be set from 20 to 450 Hz. To achieve maximal contraction in the abdominal muscles, the participant will be asked to perform a forced exhalation maneuver, which will be held for 3 seconds and repeated 3 times. Then, 15% of this contraction will be considered as submaximal and should be maintained throughout the recording.

For stimulation, a double-cone coil will be used. This coil is ideal for stimulating the motor parts of the trunk muscles. It will be placed in the M1 region, as evidence suggests that this point is the best for stimulating cortical pathways and motor nerves, resulting in better-evoked potentials. Based on previous studies, the motor cortex related to trunk muscles is recommended to be 2 cm lateral from the midline and 2 cm anterior to the vertex. Stimulation will be applied on the side opposite to the area of the back with the most pain. The coil will be positioned at a 45-degree angle to the anteroposterior axis to apply a current from back to front.

Initially, the active motor threshold will be determined. The active motor threshold is the lowest TMS intensity that generates a motor potential with a minimum amplitude of 100 µV in at least 5 out of 10 trials. Since recording occurs during isometric muscle contraction, it is termed "active." Typically, the initial stimulation intensity is set at 25% of the maximum output of the device and then gradually increased by 2% until the desired recording characteristics are achieved. The distance between the scalp and the coil will be less than 5 mm.

After determining the active motor threshold, the coil intensity will be set to 120% of the active motor threshold, and the amplitude of the resulting evoked potential will be measured. The amplitude of the active motor evoked potential will be defined as the difference between the highest peak and the lowest trough.

[figure not shown]

Fig 3. Motor-evoked potentials

**17-1-2. Clinical Assessments**

**17-1-2-1. Trunk Motor Control**

To assess trunk motor control, six tests designed by Luomajoki, which have a high validity (0.6), will be used. These tests are reliable tools for diagnosing disorders in lumbopelvic control. First, the examiner explains how to perform the movement and asks the individual to do it. If the movement is not performed correctly or the person does not understand how to perform it, the examiner will attempt to correct the movement with additional explanations. If the movement is still not performed correctly in the second attempt, the examiner will demonstrate the correct movement. If the individual cannot perform the movement correctly after the second attempt, they will receive a score of 1, and if performed correctly, a score of 0. A score of 0 indicates that all tests were performed correctly, while a score of 6 means none of the tests were performed correctly. Generally, each movement is allowed to be performed three times.

**17-1-2-2. Disability Level**

To assess disability, the Persian version of the Oswestry Disability Index questionnaire will be used. This questionnaire is designed to evaluate functional disability in individuals with low back pain and includes ten sections, such as pain intensity, personal care, walking, sitting, and others. In each section, individuals receive a score from 0 to 5. The total score is calculated numerically. A score of 0-4 indicates no disability, 5-14 indicates mild disability, 15-24 indicates moderate disability, 25-34 indicates severe disability, and 35-50 indicates complete disability (30). The questionnaire is available in Appendix 3.

**17-1-2-3. Pain Level**

To evaluate pain intensity, the Visual Analog Scale (VAS) will be used. This scale consists of a 10 cm line, where the individual rates their pain from 1 to 10. Zero represents no pain, and ten represents unbearable pain (48). This scale is a discrete quantitative measure used to assess changes in pain intensity before and after interventions.

**17-2. Treatments**

After the initial assessment, individuals will be randomly assigned to one of two groups. The sequence will be generated using the website randomization.com with a balanced block randomization method. The block size will be 4. To ensure allocation concealment, sealed and numbered envelopes will be used, which will be provided to participants by the secretary. The treatment period for both groups will be 12 sessions, three times a week. After the treatment period, evaluations will be conducted again.

Due to the inclusion of a sham treatment, participants will be blinded, but blinding of the therapist or evaluator will not be possible.

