**9. Study Type**

Randomized, single-blind clinical trial

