**17-2-4. Transcranial Electrical Stimulation**

To apply electrical current, the tDCS device model Neurostim2 from Medina Teb Gostar will be used. Before the patient's arrival, all equipment including electrodes, normal saline, stimulator, cables, elastic bands, and measurement tape will be inspected to ensure they are in good condition and free of defects or damage. The patient will sit on a chair, and the scalp will be examined for any lesions. The researcher will ask the participant to report any skin irritation from the previous session or anything else that would exclude them from the study.

Initially, the electrodes will be placed in sponges soaked with normal saline, and the area of stimulation will be cleaned with alcohol. The electrode size will be 2x4 cm. Stimulation will be applied through two active (anodal) electrodes placed on the scalp. One active electrode will be placed on the M1 region, corresponding to C3 or C4 according to the 10-20 international system. The other active electrode will be placed on the S1 region, which is 2 cm posterior to C3 or C4. Reference (cathodal) electrodes will be placed on the forehead directly above the eyebrow (Figure 6). In general, active electrodes will be placed on the opposite side of the lower back pain, and the reference electrode will be placed on the supraorbital area on the same side as the pain. The device will be set to a current intensity of 1.5 mA for 20 minutes. At the start of stimulation, there will be a 10-second ramp-up period during which the current will gradually increase to 1.5 mA. At the end, there will be a 10-second ramp-down period during which the current will gradually decrease and the device will turn off. Overall, considering the size of the active electrodes, the average current density under these electrodes will be 0.188 mA per square centimeter. The participant will be informed that they might experience a tingling or itching sensation, and the patient will be continuously monitored throughout the treatment. In the sham group, the electrodes will be placed similarly to the intervention group. The device will be turned on, and current will be applied for only 10 seconds, during which the participant will feel a tingling sensation, and then the current will be turned off. The duration of the current application in the sham group will also be 20 minutes (32).

[figure not shown]

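### The allocation envelopes are routed to the participants, the only blinded party, and no stated safeguard keeps the arm hidden from them

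*Protocol*

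**What the plan says.** Section 9 describes the study as a "Randomized, single-blind clinical trial". Section 17-2 covers both allocation and blinding. After the initial assessment, patients are randomised in blocks of 4. For allocation concealment, the section says that "sealed and numbered envelopes will be used, which will be provided to participants by the secretary". On masking, it says that "participants will be blinded, but blinding of the therapist or evaluator will not be possible".

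Masking of the participant rests on the sham procedure in section 17-2-4: "In the sham group, the electrodes will be placed similarly to the intervention group", with a brief current that is then switched off. Sections 3 and 4 list lumbar movement control, disability and pain as primary. Pain is a VAS (section 17-1-2-3), "where the individual rates their pain from 1 to 10". Disability is the Persian Oswestry questionnaire (section 17-1-2-2).

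**The concern.** Allocation concealment and blinding are separate protections. A sealed, numbered envelope keeps the next assignment from whoever enrols the patient. It serves blinding only if it is later opened by someone entitled to know the arm. The only recipient section 17-2 names is the one person who must not know it. The therapist, who has to know whether to deliver real or sham current, is not named as a recipient.

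Both arms receive the same exercises and differ only in the stimulation, so the comparison needs both groups to hold similar expectations. Participant blinding is the only masking in the trial. If patients learned their arm, the between-group difference in self-reported pain and disability would mix any effect of the current with an expectation effect, and the single-blind description would not be accurate. Section 6 would use the between-group result either to recommend the combined treatment or to favour exercises alone. Pain is also the outcome on which section 13 bases the sample size.

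**Working it through.** No arithmetic decides this point. The check sets the relevant statements side by side.

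1. **Who receives the envelope?** Section 17-2: the participant, from the secretary. No other recipient is named.
2. **What is the envelope for?** Section 17-2: allocation concealment. Ordinarily such an envelope holds the assignment, but the protocol does not describe the contents.
3. **Who must not know the arm?** Section 17-2: the participant. Therapist and evaluator are excluded from blinding, which agrees with the single-blind label in section 9.
4. **Who needs to know the arm?** Whoever operates the stimulator, since section 17-2-4 prescribes different current delivery for the two arms. That person is not mentioned in the envelope sentence.
5. **Is there a safeguard elsewhere?** Sections 17-2-1, 17-2-2 and 17-2-4 describe the two treatments and the stimulation procedure. None says that the envelope is carried unopened, that someone else opens it out of sight, or that it holds only a code.
6. **When would disclosure occur?** Randomisation follows the initial assessment, so baseline ratings are unaffected. The arm could be known before the first of the 12 sessions and therefore at the assessment 24 to 48 hours after the last one.
7. **Which outcomes are exposed?**
   - VAS pain and the Oswestry questionnaire depend on the patient's own report. These are two of the three primary outcomes.
   - Movement control is scored by an examiner (section 17-1-2-1), and section 17-2 already concedes that the evaluator is unblinded. Its main weakness therefore lies elsewhere.
   - The sensory and motor evoked potentials are instrument recordings, not self-ratings.

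Steps 1, 3 and 4 give the result: the stated route passes through the one party to be kept blind and omits the one party who needs the information. Step 5 shows that nothing written removes the risk. Steps 2 and 5 also set the limit of the claim, because neither the contents nor the opener is stated.

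**The case against.** The strongest reply is that no contradiction has been shown. A sealed envelope that the patient carries unopened to the therapist, or one that holds a neutral code, fits both the envelope sentence and the statement that participants are blinded. The wording may simply be loose. This part stands: a reader might infer that patients are told real or sham, but that needs two facts the protocol does not give, namely what is inside the envelope and who opens it. Part of the problem is indeed an omission. What remains is that the protocol does fix a route, and that route exposes the trial's only masking for no gain when a safer one is equally easy. Handling of envelopes is trial conduct, so it cannot be left to an analysis plan.

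A reader might also try to size the bias against the planned effect. With f = 0.473 and two equal groups, d = 2 × 0.473 = 0.946, and an assumed shift of 0.3 to 0.5 SD would be 0.3/0.946 = 32% to 0.5/0.946 = 53% of it. The documents give no such shift, so the percentages only restate the assumption. The denominator is uncertain too. If f refers to group means averaged over the before and after measurements, a bias acting only afterwards counts half: 0.15/0.946 = 16% to 0.25/0.946 = 26%. No figure of this kind should be quoted.

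Finally, section 12 gives a study period of March 2022 to August 2023, and section 13 says that 34 participants were recruited. If enrolment is over, new wording cannot change conduct. That affects which remedy applies, not whether the point holds.

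**Conclusion.** The point holds as a defect in a stated procedure. The allocation envelope is routed to the only blinded party, with no written safeguard, so the step as written can disclose the arm before treatment starts. Every participant randomised under that sentence passes through it. The consequence falls mainly on VAS pain and the Oswestry score.

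The conclusion assumes only the ordinary meaning of the sentence, that participants are handed the envelopes. It does not establish that anyone was unblinded, and the size of any bias cannot be derived from the documents. If the envelopes held only a code, or were always opened by the therapist out of sight, the concern is resolved once the protocol or the trial report says so.

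**What to change.** Replace the envelope sentence in section 17-2 with wording to this effect: once the baseline assessment is complete, the secretary gives the next numbered envelope, unopened, to the person operating the stimulator, who opens it out of the participant's sight; the participant never sees its contents. A neutral code inside the envelope could be added as a further safeguard, but is not needed if this route is followed.

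If enrolment is already complete, leave the historical procedure as it was and document it: who opened the envelopes, where, and what they contained. If participants could see their arm, qualify the single-blind description and interpret the pain and disability comparisons accordingly.

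The cost is one sentence in the protocol, or a short statement in the report. No staff, visits or patients are added, and nothing in the treatment changes.

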**4. Analytical Objectives**

**Primary:**

- To compare the average level of lumbar movement control in the groups (intervention and control), between before and after the intervention.
- To compare the average level of lumbar movement control between the groups (intervention and control) before and after the intervention.
- To compare the average level of disability in the groups (intervention and control), between before and after the intervention.
- To compare the average level of disability between the groups (intervention and control) before and after the intervention.
- To compare the average level of pain in the groups (intervention and control), between before and after the intervention.
- To compare the average level of pain between the groups (intervention and control) before and after the intervention.

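### The protocol rules out blinding the evaluator without giving a reason, which exposes one primary outcome to scoring bias; the fixed block of 4 also makes allocation partly predictable to anyone who knows the block size and the earlier assignments

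*Protocol*

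**What the plan says.** Section 9 calls the study a "Randomized, single-blind clinical trial". Section 17-2 explains what that means: "participants will be blinded, but blinding of the therapist or evaluator will not be possible". No reason is given for either role.

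On allocation, section 17-2 says that after the initial assessment "individuals will be randomly assigned to one of two groups". It continues: "The sequence will be generated using the website randomization.com with a balanced block randomization method", and "The block size will be 4". No stratification is mentioned. For concealment, "sealed and numbered envelopes will be used, which will be provided to participants by the secretary".

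Section 4 lists lumbar movement control first among the primary analytical objectives: "To compare the average level of lumbar movement control between the groups (intervention and control) before and after the intervention". Section 17-1-2-1 describes how it is scored. The examiner explains each of six movements, corrects and demonstrates where needed, and then decides: "If the individual cannot perform the movement correctly after the second attempt, they will receive a score of 1", otherwise 0. The other two primary outcomes are a visual analogue scale for pain (17-1-2-3) and the Oswestry questionnaire for disability (17-1-2-2).

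**The concern.** A sham-controlled trial normally allows the outcome assessor to be kept unaware of the arm, because the participant cannot reveal it. This protocol declares that impossible without explanation. For movement control, the person who may know the arm both coaches the participant and gives the verdict. A small and quite unconscious leaning on borderline tests would go straight into the between-group difference of a primary outcome.

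The second issue is predictability. A short, constant block size written in the protocol, combined with unblinded staff, lets an informed person work out some assignments before they are made. Sealed envelopes do not prevent this, because prediction needs no opened envelope. If that person also influences who enters and when, the arms may differ at entry. Baseline is scored before assignment, so an anticipated arm could also colour baseline scores.

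A smaller matter is the envelope sentence. Read literally, it sends the allocation to the only blinded party.

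**Working it through.** **Does the design require the evaluator to know the arm?** The relevant statements, side by side:

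- Baseline assessment comes before assignment (17-2), so the arm does not yet exist when baseline is scored.
- Both arms do the same exercises over 12 sessions (17-2-1 to 17-2-3).
- Electrodes are placed in the sham group as in the real group (17-2-4).
- Participants do not know their arm (17-2).
- The only reassessment is 24 to 48 hours after the last session (17 and 17-1), apart from any stimulation.

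None of these gives the scorer knowledge of the arm. The scorer would need it only if the same person also set the stimulator, and the protocol does not say that this is so. The claim of impossibility is therefore unsupported for the evaluator. For the therapist the question stays open: it depends on whether the device has a coded sham mode, which is not stated.

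**Which primary outcomes are exposed?** Movement control is judged by the examiner. Pain and disability are reported by blinded participants. That is one of three.

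**How predictable is the allocation?** The protocol gives no figure of its own to reproduce. Inputs are two arms, balanced blocks of 4 (17-2) and 34 participants (section 13). The predictor is assumed to know the block size and every earlier allocation.

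There are 6 equally likely blocks with two of each arm.

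- *Certain positions.* Position 4 is always certain. Position 3 is certain only if the first two were alike, which has probability 2/6 = 1/3. Expected per block: 1 + 1/3 = 1.33 of 4, or 33.3%.
- *34 participants* make 8 full blocks plus 2 people. Neither of the last two positions can be certain. Expected: 8 × 4/3 = 10.7, and 10.7/34 = 31.4%. Each full block has 1 or 2 certain positions, so the range is 8 to 16 (23.5% to 47.1%).
- *Best guess.* Success by position is 1/2, then 2/3, then 1/3 × 1 + 2/3 × 1/2 = 2/3, then 1. The sum is 17/6, and 17/6 ÷ 4 = 70.8% per full block. Over 34: (8 × 17/6 + 1/2 + 2/3)/34 = 23.83/34 = 70.1%, against 50% under simple randomisation.

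**What would varying blocks change?** A simulation (1,500 lists of 34; the predictor knows the set of possible sizes and all earlier allocations) gives:

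| Scheme | Certain | Best guess correct |
|---|---|---|
| Fixed 4 | 31.4% | 70.1% |
| Mixed 4/6 | about 5% | about 69% |
| Mixed 2/4/6 | about 4% | about 70% |

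Varying the size removes most of the certainty but hardly any of the advantage in guessing. Withholding past allocations addresses both.

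**The case against.** Single-blind status is declared openly, and blocks of 4 with sealed envelopes are a weaker choice, not an error. The sample size rests on pain, which blinded participants rate themselves. The protocol gives no staffing, so a separate scorer may not have been available. All of this is fair. It limits the size of the point and is why the fix is conditional on existing roles. It does not supply the missing reason for leaving the evaluator unmasked.

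Some stronger readings are tempting, but the protocol does not support them:

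- *A third of allocations are known in advance.* This holds only for someone who has the block size and all earlier assignments, and it harms the trial only if that person influences enrolment or baseline scoring. The protocol has the secretary handle the envelopes and never says who enrols.
- *The envelopes unblind participants.* The text does not say that participants open them or that the contents name the arm. Carrying a sealed envelope to the therapist would fit both the concealment and the blinding statements. The wording needs clarifying, no more.
- *The scoring bias can be put in points.* The protocol gives no rate of borderline tests and no standard deviation, so any figure would be invented.
- *The motor thresholds are equally exposed.* They are secondary, and section 17-1-1-2 fixes a numerical criterion (at least 100 µV in 5 of 10 trials) and a 2% step.
- *Movement control should be demoted to secondary.* An unmasked assessment calls for a label and cautious interpretation, not a changed outcome hierarchy.

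**Conclusion.** The point stands in two parts of unequal weight. The main one is that the protocol asserts without a reason that the evaluator cannot be blinded, although its own design leaves room for it; one of three primary outcomes is exposed to scoring bias of unknown size. The lesser one is that the fixed block of 4 would let a fully informed person foresee an expected 31% of the 34 allocations (about 10.7; range 8 to 16) and guess about 70%. Those figures are exact under the stated assumptions about what the predictor knows. Whether anyone was in that position is not stated, so selective enrolment remains a risk.

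It is also unclear how much can still be changed. Section 13 speaks of recruitment in the past tense and section 12 ends the study in August 2023, while most of the protocol is in the future tense.

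**What to change.** In section 17-2:

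1. Replace the clause on the evaluator by a rule that whoever scores the post-treatment tests is not told the arm and did not set the stimulator, where existing roles allow. Where they do not, label movement control as assessed unmasked when it is reported and interpreted, and keep it as a primary outcome.
2. For any participants still to be randomised, use randomly varying block sizes (for example 2, 4 and 6) that are not disclosed to staff who enrol, treat or assess. Keep past allocations from whoever enrols; this matters more than the block sizes.
3. Reword the envelope sentence so that the secretary gives an opaque envelope, after baseline, to the person who sets the device and not to the participant.

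The cost is a new list for remaining participants, some re-assignment of roles and a slightly larger possible imbalance between arms. If enrolment is complete, only the scoring rule for outstanding assessments and the unmasked label still apply.
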